### Interim analyses {21b}

No additional analyses are planned.

### Methods for additional analyses (e.g., subgroup analyses) {20b}

No additional analyses are planned.

### Methods in analysis to handle protocol non-adherence and any statistical methods to handle missing data {20c}

All analyses will be based on the intention-to-treat (ITT) principle such that participants will be analyzed in the arm to which they were randomized, regardless of intervention exposure. We will perform sensitivity analyses to address loss to follow-up (LTFU). We will summarize baseline characteristics by LTFU status separately by study conditions to identify possible predictors of LTFU and whether they differ by condition. Covariates that are predictive of LTFU will be included in regression models to assess any changes to conclusions based on an assumption of missing-at-random dependent on covariates. Pattern mixture approaches will be used to explore possible missing-not-at-random mechanisms [87].

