### Outcomes {12}

The primary outcome measure is viral suppression at 12 months, determined by HIV viral copies per milliliter of blood. Viral suppression will be reported as a dichotomous variable with the threshold for viral suppression defined as < 50 copies/mL, as determined by the Abbott Alinity assay (Sensitivity Limit of Detection 20 copies/mL).

The following secondary outcome measures will be assessed at baseline, 4, 8, and 12-month timepoints:ART adherence:◦ Dried blood spots measuring levels of tenofovir-diphosphate (TFV-DP) (at 12 months)◦ Medical record abstraction of pharmacy visits and pharmacy refill data◦ Adapted Adult AIDS Clinical Trials Group self-report measure of adherence [74, 75]HIV care engagement (medical record abstraction):◦ Missed visits (# of monthly visits missed and binary indicator of any missed monthly visit)◦ Visit adherence (proportion of visits kept)◦ Gaps in care (whether > 90 days have elapsed between visits)◦ Visit constancy (# of 90-day intervals with > 1 completed visit).◦ Mental health mediators will be assessed by the following measures (all timepoints):Post-Traumatic Stress (PTSD Checklist-Civilian version for the DSM-5 (PCL-5) [76]Coping [45], adapted from [77–81].

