### Participant timeline (Table 2) {13}

#### Sample size {14}

Our enrollment target is 350, which will allow detection of intervention effects on viral suppression at 12-month follow-up. Based on data from our preliminary studies [66] and corroborated by national estimates [32], we expect that 57% of women who are newly initiating ART and randomized to the PST condition will be virally suppressed at the 12-month follow-up. With 350 women randomized equally to both conditions, we will have 80% power with a two-tailed alpha level of 0.05 to detect differences between a proportion of 57% in the PST condition and 73% in the ImpACT + condition. This power calculation assumes we will retain 80% of participants over the study period. In the pilot, we were able to successfully retain 80% of all participants (83.3% of newly initiating participants) for the duration of the study [45].

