## Data collection and management

### Plans for assessment and collection of outcomes {18a}

Participants will go through the full trial informed consent process at baseline, after which RAs will verbally administer a battery of psychological assessments and other self-report measures in isiXhosa. Independent assessors will administer the same battery at 4-, 8-, and 12-month follow-up assessments. Assessments will take approximately 60 min and will be conducted in a private room at the clinic. Study staff will clarify any questions and refer participants who indicate high suicide risk during the interviews to the medical officers for further assessment and referral. Blood samples to measure viral load and ARV adherence via DBS will also be collected at all follow-up assessments. Relevant HIV care data will be abstracted from participants’ medical records.

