### Plans to promote participant retention and complete follow-up {18b}

Study staff will emphasize the importance of attending all intervention sessions and assessment appointments. We will collect detailed contact information for participants and close contacts. We will reschedule appointments as needed and follow-up with participants who miss sessions and assessments.

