## Statistical methods

### Statistical methods for primary and secondary outcomes {20a}

To assess intervention effects on the primary outcome (viral suppression), we will compare the proportion of participants achieving HIV viral suppression at 12 month follow-up across study conditions by estimating a risk ratio and obtaining confidence intervals using robust error variances with a modified Poisson model and log link [83]. We will similarly obtain risk ratio estimates to assess intervention effects on the secondary outcomes (i.e., measures of ART adherence and care engagement) using the modified Poisson approach appropriate distribution and link function based on the outcome examined.

To examine the underlying mechanisms of the intervention effects on primary and secondary outcomes at 12 months, we will evaluate the effects of ImpACT + , compared to PST, on hypothesized mediators (e.g., levels of traumatic stress and avoidant coping). Our analytic approach will incorporate the appropriate distribution and link function depending on the distribution of these mediators. We will then examine the effect of both mediators on viral load. If the product of these two paths is greater than zero, this will serve as evidence of mediation [84]. The same approach will be utilized to evaluate the degree to which changes in traumatic stress and avoidant coping mediate intervention effects on secondary outcomes (ART adherence and care engagement).

Finally, qualitative data will be analyzed using a thematic analysis approach [85]. Memos will be written for each transcript to synthesize the emerging themes across the CFIR domains. Themes will be identified via consensus discussion after independent review of transcripts and textually coded using NVivo and/or ATLAS.ti software by multiple coders. Data display matrices will be used to examine commonalities and differences across informants [86]. A diagrammatic visual, overlaid on the CFIR framework [53] will highlight the potential barriers and facilitators to full-scale implementation.

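### The planned missing-at-random analysis uses baseline predictors of loss and gives no role to the 4- and 8-month viral loads, so the 12-month risk ratio is exposed to loss that depends on suppression differently by arm

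*Protocol article*

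**What the plan says.** All references are to the Protocol article.

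- **Outcome (Outcomes {12}).** "The primary outcome measure is viral suppression at 12 months, determined by HIV viral copies per milliliter of blood", dichotomised at 50 copies/mL.
- **Primary model (Statistical methods for primary and secondary outcomes {20a}).** The arms are compared at 12 months by "estimating a risk ratio and obtaining confidence intervals using robust error variances with a modified Poisson model and log link". No imputation, weighting or repeated-measures model is attached to it.
- **Size (Sample size {14}).** "With 350 women randomized equally to both conditions, we will have 80% power with a two-tailed alpha level of 0.05" for 57% against 73%. "This power calculation assumes we will retain 80% of participants over the study period".
- **Missing data ({20c}).** "We will perform sensitivity analyses to address loss to follow-up (LTFU". Baseline characteristics are summarised by loss status within arm to find predictors of loss. Then "Covariates that are predictive of LTFU will be included in regression models to assess any changes to conclusions", under an assumption of missing at random given those covariates. Pattern-mixture methods are to explore missing-not-at-random mechanisms.
- **Interim data (Plans for assessment and collection of outcomes {18a}).** "Blood samples to measure viral load and ARV adherence via DBS will also be collected at all follow-up assessments", which means months 4, 8 and 12.
- **Retention (Plans to promote participant retention and complete follow-up {18b}).** Staff will "follow-up with participants who miss sessions and assessments".

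Neither {20a} nor {20c} gives the 4- and 8-month viral loads a role, and {20b} plans no further analyses.

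**The concern.** A woman with no 12-month sample may already have a viral load from month 8 or month 4. That is closer to her missing outcome than any baseline trait. The stated remedy cannot use it. Adding covariates to the outcome regression still excludes every woman without an outcome, and it corrects only for loss explained by those covariates. Putting an interim viral load into that regression would not help either, because it is measured after randomisation and may carry part of the treatment effect. Imputation or weighting is needed to use it properly.

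Loss could plausibly relate to suppression differently in the two arms. ImpACT+ has six weekly sessions and six monthly check-ins, 12 scheduled contacts; PST has three sessions. The check-ins start after the 4-month assessment, when PST has no intervention contact scheduled. Missed sessions prompt follow-up by staff, so ImpACT+ offers more occasions to bring a disengaging woman back. At stake is the trial's headline estimate, when data that could reduce the bias are already being collected.

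**Working it through.** **1. The plan's own figure.** Inputs from {14}: 57% and 73%, two-sided alpha 0.05, 80% power, 80% retained, 350 randomised 1:1.

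- Pooled-variance formula: n per arm = [1.96·√(2·0.65·0.35) + 0.8416·√(0.57·0.43 + 0.73·0.27)]² / 0.16² = 138.3, so 139.
- Inflated for loss: 278 / 0.8 = 347.5, so 348, against 350 stated.
- Power at 0.8 × 175 = 140 per arm is 0.805, against 0.80 stated.

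The figure reproduces. It also shows that the trial is sized for an analysis of about 280 women with an outcome.

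**2. When the complete-case risk ratio is biased.** Let p be the true proportion suppressed in an arm, R retention and Y suppression. The complete-case proportion is p × P(R | Y=1) / P(R). The risk ratio is therefore multiplied by the between-arm ratio of P(R | Y=1) / P(R). If that quantity is equal in both arms, it cancels.

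Check: suppose 20% are lost per arm and every lost woman is unsuppressed. The true proportions are 0.8 × 0.57 = 45.6% and 0.8 × 0.73 = 58.4%, and the complete-case proportions are 57% and 73%. The risk ratio is 1.28 either way.

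**3. Equal loss, equal suppression among the lost.** Assumptions: 20% lost per arm, a share q of lost women suppressed in both arms, true 57% and 73%. Complete-case proportion = (p − 0.2q) / 0.8.

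- q = 0.1: 0.6875 and 0.8875, RR 1.29.
- q = 0.4: 0.6125 and 0.8125, RR 1.33.

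The true value is 1.28, so the bias is small.

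**4. Loss differing by arm, no true effect.** Assumptions: 57% in both arms, retention 75% (PST) and 85% (ImpACT+), q of lost women suppressed. PST = (0.57 − 0.25q) / 0.75; ImpACT+ = (0.57 − 0.15q) / 0.85.

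- q = 0.1: 0.727 and 0.653, RR 0.90.
- q = 0.3: 0.660 and 0.618, RR 0.94.

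Here the bias runs against ImpACT+.

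**5. Equal overall loss, dependence in one arm only.** Assumptions: P(suppressed at 12 months) is 0.85 if suppressed at month 8 and 0.25 if not; 20% are lost in each arm. The month-8 proportions that give 57% and 73% are (0.57 − 0.25)/0.6 = 0.533 and (0.73 − 0.25)/0.6 = 0.80.

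- Dependence in PST only (10% of suppressed and 31.4% of unsuppressed women lost): PST is observed at 0.610, RR 0.73 / 0.610 = 1.20.
- Dependence in ImpACT+ only (10% and 60%): ImpACT+ is observed at (0.72·0.85 + 0.08·0.25) / 0.80 = 0.79, RR 0.79 / 0.57 = 1.39.
- Both together: 0.79 / 0.610 = 1.30.

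Equal retention therefore does not by itself protect the estimate, and the bias can go either way. If loss depends only on the month-8 result and arm, using that result removes the bias. That follows from the set-up and is not evidence about this trial.

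**The case against.** **The complete-case reading is an inference.** This is correct; no sentence says it. But {20a} fixes a 12-month-only model, {14} computes power on the women retained, and {20c} confines loss to sensitivity analyses. No other reading fits all three. The 20% is a planning assumption, not an observed loss.

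**Loss related to suppression need not bias a risk ratio.** This stands, as step 2 shows. A reader might infer that any such loss biases the result, or point to step 3, where the risk difference moves from 16 to 20 points. The plan estimates a risk ratio, and there the shift is small. Material bias needs dependence that differs by arm. The article gives no arm-specific retention, so steps 4 and 5 are illustrations.

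**Safeguards exist.** Predictors of loss are compared by condition, pattern-mixture analyses are planned, and the monitoring board reviews retention by condition. These would help to reveal a problem. None is described as using the interim viral loads, and none changes the primary estimate.

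**The analysis plan may add detail.** Death coding, visit windows and the imputation specification can properly be left to it, and their absence here is no fault. The article does, however, publish the hierarchy and the source of the covariates; the point concerns that stated choice.

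**Tempting stronger readings.** Counting missing women as unsuppressed gives 45.6% against 58.4% and 67% power, from which a reader might infer an underpowered trial. Nothing in the plan makes that analysis primary. A reader might also expect routine clinic viral loads to fill the gaps. Consent covers record review, but the abstraction described lists pharmacy and visit data and no routine viral loads.

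**Conclusion.** The point holds in limited form. The stated missing-at-random analysis is weaker than the trial's own data allow, because it relies on baseline predictors and omits viral loads measured in the same women at 4 and 8 months. The consequence is possible bias in the primary risk ratio, in either direction, if loss depends on suppression differently by arm. Under the assumed retention of 75% and 85% it is 0.90–0.94 for a true 1.00. With equal loss and equal suppression among the lost it is only 1.29–1.33 for a true 1.28. These sizes rest on assumed loss patterns, and the documents do not show that such loss will occur.

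The sample size and the 80% power are correct as stated. The intention-to-treat statement is not contradicted either: {20c} defines it as analysis by randomised arm, which does not settle how missing outcomes are treated. The change is worth making because it is cheap and concerns the primary outcome.

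**What to change.** Multiply impute missing 12-month suppression separately by arm. Use the 4- and 8-month viral loads, the randomisation factors (initiation status, clinic, pregnancy), baseline predictors of loss and the care-engagement data from medical records. Then fit the planned modified Poisson model to all 350 randomised women and combine the results across imputations. Make this the primary analysis in {20a}. At minimum, let it replace the baseline-covariate missing-at-random analysis in {20c}. Keep the complete-case and pattern-mixture analyses as sensitivity analyses, and fix the specification before allocation is revealed.

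The cost is analysis-plan wording and imputation code, with no new visits or blood draws. The randomisation factors form 3 × 4 × 2 = 24 cells, so they should enter as main effects. The downside is reliance on an imputation model and on missing at random given the interim data. Women lost before month 4 have no interim viral load and would be imputed from baseline and record data alone, so the pattern-mixture analysis remains necessary.

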### Plans to give access to the full protocol, participant-level data, and statistical code {31c}

The primary investigators, project coordinator at CUIMC, project director at UCT, and statisticians at CUIMC will be given full access to trial data.

## Oversight and monitoring

### Composition of the coordinating center and trial steering committee {5d}

A formal coordinating center is not needed for this single-site study.

Daily support for the trial is provided by:

Principal Investigators: provides scientific oversite and responsibility.

Clinical supervisor: supervises nonspecialists interventionists.

Clinical psychologist: emotionally supports field staff.

Project director: oversees daily trial activity and supervises control.

Senior research assistant: supervises research assistants and field data collection.

Project coordinator: organizes data collection, ensures data quality, trial registration, and annual reports.

Research assistants: take informed consent, administer assessments, and schedule appointments.

The study team meets weekly.

### Composition of the data monitoring committee, its role, and reporting structure {21a}

Throughout the course of the trial, all protocol modifications will be reported to the University of Cape Town’s Human Resources and Ethics Committee (HREC), Columbia University IRB, and the Data Safety and Monitoring Board (DSMB). The DSMB is comprised of independent, experienced, and highly qualified members who are free of any professional or financial conflict of interest with the study project and investigators. The DSMB reviewed the study protocol and data monitoring procedures prior to trial recruitment and approved the data monitoring plan for the remainder of the study. The DSMB will meet on an annual basis to review study progress, enrollment, randomization, and retention data (including reasons for dropout and retention by study condition); data integrity; and patient safety data, including reported adverse events and protocol deviations.

### Adverse event reporting and harms {22}

All adverse events will be recorded. We will follow the reporting guidelines as set out by UCT HREC, CUIMC IRB, NIMH, and our DSMB.

### Frequency and plans for auditing trial conduct {23}

CUIMC IRB and UCT HREC will meet annually to review trial progress and conduct throughout the trial period. In addition, all adverse events and protocol deviations will be reported according to IRB And HREC guidelines.

### Plans for communicating important protocol amendments to relevant parties (e.g., trial participants, ethical committees) {25}

We will seek approval from CUIMC and UCT HREC prior to implementing any protocol amendments, and to NIMH when required.

### Dissemination plans {31a}

In addition to academic manuscripts and presentations, we will collaborate with the City of Cape Town and HIV and policy makers to disseminate lessons learned in our research. If effective, we will work towards full-scale implementation of ImpACT + in the region and be available to adapt the intervention for other global settings.

## Discussion

There is a substantial treatment gap for women living with HIV (WLH) who have experienced sexual trauma. The scientific evidence on the coexisting burdens of HIV infection and sexual trauma among women in South Africa, and the well-documented drop-off from linkage to HIV care to viral suppression across the HIV care cascade [32, 43, 88] demonstrate the need for evidence-based, scalable interventions that address HIV care engagement in this context. Specifically, there is an urgent need to address the psychological sequelae of HIV, sexual trauma, and mental health, which can significantly impact HIV treatment adherence.

This trial is unique for several reasons. Firstly, despite robust evidence highlighting the adverse impact of sexual trauma on HIV treatment adherence and care engagement, we have not identified any full-scale randomized controlled trials demonstrating the effectiveness of trauma-focused psychological and behavioral interventions to improve biological outcomes in South Africa, or other low- and middle-income countries (LMIC) [89, 90]. This study aims to determine whether a mental health intervention to reduce avoidant coping and traumatic stress in comparison to a high-quality control intervention condition can improve clinical HIV outcomes, including viral suppression (primary outcome) and ART adherence and HIV care engagement (secondary outcomes). This type of holistic approach is not only key to improve individual outcomes, but also to motivating health departments to increase resources dedicated to integrating mental health services into chronic disease settings. As the revised UNAIDS care cascade goals move towards even higher rates of ART initiation, care retention, and viral load suppression, health systems will need to develop ways to address important behavioral and psychosocial determinants of treatment failure.

The second important innovation is that this study will explore whether increased likelihood of viral suppression is mediated by improvements in mental health. Demonstrating that improvement in psychological symptoms mediates the effectiveness of a behavioral intervention to improve adherence will strengthen the case for mental health services to be integrated in primary health care settings, particularly in the context of large mental health treatment gaps in LMICs [91]. In the absence of adequate numbers of trained psychologists and other mental health specialists, the use of culturally appropriate, manualized, and task-shared approaches becomes even more compelling. Given the sensitivity required to broach topics of sexual trauma and the potential for vicarious trauma, ImpACT + is intended for delivery by trained and supervised interventionists. Nurses and social workers are frequently employed in primary healthcare settings and are therefore the most likely candidates for interventionists. These cadres represent a key resource in the South African primary health care system, as well as in many other LMIC.

The third innovation is that we will report on critical implementation outcomes within the context of primary health care. Qualitative data from interventionists, facility managers, local stakeholders, and WLH with lived experience of trauma will inform potential and plans for implementation. Therefore, this trial will systematically evaluate feasibility and acceptability in addition to primary effectiveness. The implementation outcomes of this study will be presented to key stakeholders for consideration for adoption in health system training and capacitation programs. Our goal is to contribute to future policy and practice in the wider health care system.

Despite the strengths of this trial, implementation challenges may arise. We anticipate some difficulties in recruiting participants experiencing traumatic stress in busy clinic settings. To address this, we will work collaboratively with staff involved in HIV care at our study sites to established routine referral systems. Confidentiality and sensitivity will be paramount to the success of this trial. Participant retention is a second potential challenge. We anticipate that almost all of our participants will live in peri-urban areas and may therefore struggle to attend intervention sessions or scheduled assessments for reasons associated with informal employment, illness, and interprovincial migration. To address this, our study team will endeavor to establish collaborative relationships with participants. Moreover, we aim to enhance retention through maintenance of detailed contact information and using clinic records to align intervention-related visits with scheduled clinic appointments. Lastly, we aim to pre-empt potential vicarious trauma, compassion fatigue, or emotional distress among field staff by holding regular debriefing sessions with a clinical psychologist.

It must be acknowledged that even if this intervention is proven effective and is implemented into care settings in South Africa, it cannot address the systemic roots of sexual trauma and HIV infection. Extreme inequality linked to historic disparities impacts many upstream issues such as education, housing, and poverty. These inequalities must be addressed in order to truly improve national health outcomes [92, 93]. However, women today are living in settings that put them at increased risk for sexual violence and HIV, and they need treatment at a faster pace than is possible on a policy level. As such, we feel obligated to work towards improving current mental health needs and clinical HIV outcomes.

In summary, this trial is expected to yield important new information on psychologically informed intervention models that benefit the mental health and clinical outcomes of WLH with histories of sexual trauma. The proposed ImpACT + intervention, with its focus on building coping skills to address traumatic stress and engagement in HIV care and treatment, could have widespread impact on the health and wellbeing of individuals and communities in sub-Saharan Africa.

